#### Tertiary outcomes

##### Net survival - measured in Sanako, village B

For simplicity and to maximise precision of this measure, all nets will be sampled at 6-monthly time intervals: that is 374 of LLIN and 167 of PPF-LLIN. Direct comparisons of functional LLIN survival will be made between both net types using Kaplan-Meir analysis.

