**Methods:**

This is a cluster randomised controlled trial of net durability in Burkina Faso, with clustering at the level of the compound and includes entomological outcome measurements. Half the compounds in each village will be randomly allocated PPF-LLIN and half the LLIN. All sleeping places in a compound will be provided with one type of net. We will distribute the nets at the start of the first transmission season and follow net use at the start and end of each transmission season for 3 years. In one village, bio-efficacy and chemical content will be recorded immediately after net distribution and then at 6, 12, 18, 24, 30 and 36 months. In the other village net survivorship and fabric integrity will be recorded immediately after distribution, and then at 6, 12, 18, 24, 30 and 36 months. Routine measurements of indoor temperature and relative humidity will be made in both villages during the study. Residents will be followed for possible side effects of the PPF-LLIN by surveillance of known asthmatic subjects during the first month post-distribution and pregnancy outcomes will be monitored from antenatal clinic records.

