### Randomisation and blinding

Both types of net will be randomly allocated to compounds, with allocation stratified by compound size in both villages. In village A 6 different compounds will be sampled in each study arm at 7 sequential time points: thus, 84 compounds (42 for each study arm) will be selected randomly, without replacement, at the start of the study. The remaining compounds in the village will be randomly assigned equally to the intervention or control and will act as reserve compounds in case of withdrawal of those randomised. At each sampling time point 4 nets will be randomly selected from each of the pre-selected compounds: that is within 1 to 2 weeks of hanging and then 6, 12, 18, 24, 30 and 36 months later. As holes will be cut in the selected nets to provide netting samples for laboratory testing, the nets will be taken from the recipient and replaced with a new one of the same type: that is LLINs will be replaced with LLINs and PPF-LLINs replaced with PPF-LLINs. A total of 649 nets will be distributed in Dalamba (village A) and 541 in Sanako (village B). In cluster-randomised controlled trials it is particularly important to minimise imbalance for factors likely to be correlated with the outcome; bio-efficacy will probably be affected by net washing and possibly by the ambient temperature and humidity, this will be corrected for in the analysis. Observer bias will be reduced where feasible. Both types of nets will be of a similar shape and colour and will be blinded before distribution, see below. Thus, end-users, field workers conducting the physical integrity/survivorship surveys and technicians conducting the bio-efficacy, fabric integrity and insecticide content tests will be blinded to the type of net. A standard questionnaire will be used to collect data from the net user at each follow-up. The processes of the interventions, both for PPF-LLINS and LLINs, will be closely monitored not only for quality but also to document any bias between the clusters and villages.

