#### Secondary outcome

##### Fabric integrity - measured in Sanako, village B

Since LLIN and PPF-LLIN are manufactured with the same fibre, the same weave and are manufactured by the same company we would not expect to find a difference in fabric integrity between them. However, a control programme manager might consider replacing all the nets in an area if > 25% were of poor condition. To estimate 25% nets in poor condition with a precision of ±10%, with a design effect of 1.0 because of cluster sampling, at the 5% level of significance, assuming there are either 500 LLINs or PPF-LLINs, would require 64 nets in each arm at the last sampling time. To allow for a loss of 10% of nets per year and for operational uniformity it is simplest to maintain the study framework of 100 nets in each group to allow for loss to follow-up if net users move away or stop using their nets; in which case, we would sample four nets in twenty-five compounds in each study arm. In addition, direct comparisons will be made between both nets.

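### The village B net counts (374 LLIN, 167 PPF-LLIN) do not fit the stated allocation of half the compounds to each net type, stratified by compound size

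*Protocol article*

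**What the plan says.** Three statements fix how many nets of each type village B should hold.

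- **Abstract, Methods:** "Half the compounds in each village will be randomly allocated PPF-LLIN and half the LLIN". It adds: "All sleeping places in a compound will be provided with one type of net". The number of nets in an arm therefore follows from the sizes of the compounds allocated to it.
- **Randomisation and blinding:** "Both types of net will be randomly allocated to compounds, with allocation stratified by compound size in both villages". The same section gives the totals distributed as 649 nets in village A and 541 in village B.
- **Sample size rationale, Net survival:** in village B "all nets will be sampled at 6-monthly time intervals", "that is 374 of LLIN and 167 of PPF-LLIN".

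The fabric-integrity sample size for the same village uses a symmetric framework of 25 compounds and 100 nets per arm. Nowhere does the article give an unequal ratio for village B or comment on the uneven counts.

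**The concern.** Two equal halves of a village's compounds, balanced on size, should hold similar numbers of nets. Here one arm has more than twice as many as the other, so the stated allocation and the stated counts cannot plausibly both be right.

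Village B is the sole source of the fabric-integrity comparison (secondary) and the net-survival comparison (tertiary). What is at stake depends on the explanation:

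- If the counts are wrong, the denominators for survivorship and attrition are wrong.
- If the ratio was deliberately unequal, the abstract misdescribes the design.
- If large compounds went mainly to LLIN, compound size is associated with net type. Anything about net wear or loss that varies with compound size would then enter the comparison. The article presents no evidence on whether wear or loss does vary with compound size.

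**Working it through.** **Inputs from the article.** Village B: 374 LLIN and 167 PPF-LLIN nets, 541 in total. Half the compounds to each arm, stratified by size. One net type for every sleeping place in a compound. Fabric-integrity framework of 25 compounds per arm. Village A: 649 nets, with 84 compounds selected and others held in reserve.

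**Step 1: do the counts cover the whole village?** 374 + 167 = 541, exactly the stated total. The counts are the full distribution, not a subsample, and a misprint in only one of the two numbers would have broken the sum.

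**Step 2: how far from an equal split?**
- Expected per arm: 541 / 2 = 270.5.
- Observed LLIN share: 374 / 541 = 69.1%.
- Ratio: 374 / 167 = 2.24.
- Distance from equality: 374 − 270.5 = 103.5 nets in each arm.

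With equal numbers of compounds, LLIN compounds would need on average 2.24 times as many nets as PPF-LLIN compounds.

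**Step 3: could chance do this?** The unit of randomisation is the compound, so some imbalance in nets is expected. The number of village B compounds, the variation in their size and the number of strata are not given, so these are assumptions: 30 to 130 compounds; gamma-distributed sizes with a coefficient of variation (CV) of 0.5 to 1.0, scaled to 541 nets; half the compounds allocated to each arm within 2 or 3 size strata, or with no strata; 4,000 runs per setting. The table gives the probability of a split at least as uneven as 374:167 at CV 1.0, the value most favourable to chance.

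| Compounds | No strata | 2 strata | 3 strata |
|---|---|---|---|
| 30 | 2.8% | 0.55% | 0.02% |
| 50 | 0.48% | 0.05% | none seen |
| 84 | 0.02% | none seen | none seen |
| 100 or 130 | none seen | none seen | none seen |

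At CV 0.8 with 50 compounds the figures are 0.05% without strata and none seen with 2 or 3 strata.

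**Step 4: which rows are relevant?** A framework of 25 compounds per arm needs at least 50 compounds. In village A the mean is at most 649 / 84 = 7.7 nets per compound. If village B compounds were of similar size (an assumption), there would be about 541 / 7.7 = 70 or more. The rows from 50 upwards, with strata, are the ones that match the article.

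**Step 5: cost in precision if the split is benign.** The information relative to an equal split is 4 × 0.691 × 0.309 = 0.85, so the standard error is 1 / √0.85 = 1.08 times as large. As an illustration, assume a hazard ratio of 0.7, 200 events and no clustering: power falls from 71% to 64%. Precision is the smaller issue.

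**The case against.** **An unequal ratio may have been intended.** In the body of the article, equal numbers of compounds per arm are spelled out only for village A. For village B the randomisation section says only that allocation is random and stratified by size; the explicit half-and-half statement is in the abstract, and the 25 compounds per arm describe a sampling framework. This stands as a possible explanation. It would make the problem one of wording, and an unequal ratio that was randomised is still a valid randomised comparison. It does not remove the inconsistency, because the abstract says half in each village.

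**The probabilities rest on assumptions.** This also stands. With 30 compounds, widely varying sizes and no strata, the chance rises to about 3%. That case drops the stated stratification and has too few compounds for the fabric-integrity framework.

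**Stronger readings that the documents do not support.**
- A reader might infer that randomisation failed or that size confounds the comparison. The counts do not show this: it is one of three explanations, and nothing in the article links compound size to net wear or loss.
- A reader might take "assuming there are either 500 LLINs or PPF-LLINs" in the fabric-integrity sample size as a further conflicting count. It is a finite-population planning input: 1.96² × 0.25 × 0.75 / 0.10² = 72.03, and 72.03 / (1 + 71.03 / 500) = 63.07, which rounds up to the stated 64. It is conservative: 374 or 167 in place of 500 would give 61 or 51 nets. The planned 100 per arm exceeds all of these.
- A reader might extend the doubt to the primary outcome. Bio-efficacy is measured in village A, which these counts do not touch.

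**Adjustment for size stratum may be in an analysis plan that is not shown.** Fair. Its absence from the article is not itself the fault; it matters here because the counts raise the question of balance on size.

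**Conclusion.** The inconsistency is real. A 2.24:1 split of all 541 village B nets is not compatible with 1:1 allocation of compounds stratified by size. Under the assumed compound numbers and size variation, chance accounts for it with probability of about 0.05% or less for 50 or more compounds, and about 0.6% in the least favourable stratified case of 30. The smallest of these rest on a handful of simulated events and should be read as orders of magnitude.

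The article does not show whether the counts, the stated ratio or the working of the stratification is at fault, so the village B comparison is open to question but not shown to be invalid. Only the secondary and tertiary outcomes measured there are affected. Severity is moderate.

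**What to change.** 1. Someone outside the blinded team tabulates village B compounds and nets per arm, by size stratum, against the randomisation list.
2. Depending on the result, correct the counts under Net survival, or state the actual village B allocation ratio in the abstract and in Randomisation and blinding.
3. Account for compound-size stratum in the village B arm comparisons: a stratified log rank test or equivalent for net survival, where the article names a log rank test without stating such an adjustment, and a size-stratum term in the fabric-integrity models.
4. If the list was followed at an unequal ratio, say so; the comparison remains randomised. Only if the list was not followed should the departure be reported and the comparison qualified.

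The cost is one list check, a few corrected sentences and one stratification factor that the trial already randomises by. The fabric-integrity sample size needs no change.

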### Chemical analysis measured in Dalamba, village A

A 75% decline in the total content of either permethrin or PPF would cause concern since this is likely to impact the operational effectiveness of PPF-LLIN. The total concentration of PPF and permethrin in the fibres will be compared to the insecticidal activity overtime to examine their relationship. The manufacturers certify that the PPF-LLIN contain 2.0 g permethrin/g fibre, with range 1.5 g to 2.5 g and 1.0 g PPF g/g fibre, with range 0.75 to 1.25 g. In order to detect a 75% reduction in insecticide from 2.0 g to 0.5 g with a coefficient of variation of 0.25 (considered appropriate for factory-produced products where variation between nets is considered small) at the 5% level of significance and 80% power we will require 4 compounds in each study arm with 5 nets tested in each compound (n = 20 nets in each group). Since nets will be damaged during sampling they will be replaced with a new intact net. For this reason it is important that the date at which the net was put in place is recorded directly on each net.

### Data handling and record keeping

Entomological and environmental data will be recorded by field assistants and the clinical data by study nurses on standardised data forms. Each net will have a unique ID number and study subjects participating in the cross-sectional surveys will have their demographic surveillance number. All data recorded on individuals will be made by recording their demographic surveillance number, the village of residence and initials of the study subject; the initials will not be entered into the dataset to maintain anonymity.

Data forms will be double-entered, firstly by field staff and then by data entry staff, and the entries combined and errors corrected to produce a single dataset. This will be submitted to consistency checking by generic and study specific algorithms designed to identify sources of error. When inconsistencies occur, these will be checked against the original forms and subsequently amended in the dataset. Errors will be corrected when possible, with checking in the field when necessary and possible, to produce final datasets.

All forms with subject names and/or clinical data will be kept in a cabinet and locked when not in use; the key will be kept by the study coordinator or delegate. The electronic datasets will be password protected. Hard copies of the data will be stored for 10 years. The clinical data will be kept separately from that containing personal information. All forms and datasets, apart from those for enumeration, will identify subjects by their demographic surveillance number and initials and names will not be collected and initials will not be entered. After the collection and verification, data will be moved to data management unit in Banfora for data entry. The datasets will be password protected and only accessed by authorised study staff and the study data manager until after publication. Data will be stored for at least 10 years.

The PI will ensure that appropriate medical and research records for this study are maintained in compliance with Good Clinical Practice (GCP) and regulatory and institutional requirements. Authorised representatives of the sponsor, the ethics committee(s) or regulatory bodies may inspect all documents and records required to be maintained by the investigator. The PI, or designee, will ensure the access to facilities and the records.

### Reduction in offspring

If less than 20% of gravid females in the control group fail to lay eggs the experiment will be repeated.

General linear modelling will be used to assess the activity of the different insecticide treatments over time, adjusting for compound. Kaplan-Meier survival analysis will be used to compare treatments over time.

### Fabric integrity

Three indicators will be calculated at each survey time: 1) the proportion of torn nets, 2) the proportion of nets with holes and 3) a hole index.

Proportion of nets in poor condition (with 95% confidence interval):Numerator: total number of each type of net where the nets are not long enough to be tucked under the mattress, or are torn or badly damaged, or have more than 5 holes (finger-width, approximate diameter 2 cm)Denominator: total number of each net type found and assessed in surveyed households

Proportion of nets with any holes (with 95% confidence interval):Numerator: fabric integrity will be defined using the pHI [14] grouped into the following categories: good (pHI range 0 to 64), acceptable (pHI 65 to 642) and torn (pHI ≥ 643)Denominator: total number of each net type found and assessed in surveyed households

The hole index would be calculated as:

Hole index = (0.5 to 1.9 cm^2^ × number of size-1 holes) +(2.0 to 9.9 cm^2^ × number of size-2 holes) + (10.0 to 24.9 cm^2^ × number of size-3 holes) + (≥25.0 cm^2^ × number. of size-4 holes)

The holes will be weighted according to the average area of each hole category. For the hole size categories described above, the weights would be 1, 23, 196 and 578, which corresponds with the areas estimated on the assumption that the hole sizes in each category are equal to the mid-points.

For each net type, the mean and standard deviation as well as the median and inter-quartile range of the hole index will be determined. Comparisons between treatments at different periods will be made using generalised linear models, adjusting for compound.

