### Secondary: fabric integrity

Fabric integrity will be as defined earlier using the pHI [14] grouped into the following categories: good (pHI range 0 to 64), acceptable (pHI 65 to 642) and torn (≥643).

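### The hole index pairs classes printed as areas (cm²) with weights that fit only diameters (cm), and two companion fabric-integrity indicators are misdefined or mislabelled

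*Protocol article*

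**What the plan says.** The Fabric integrity section of the data analytical plan announces three indicators: torn nets, nets with holes, and a hole index.

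- **Hole index.** The first two terms are "0.5 to 1.9 cm^2^ × number of size-1 holes) +(2.0 to 9.9 cm^2^ × number of size-2 holes" and the last two are "10.0 to 24.9 cm^2^ × number of size-3 holes) + (≥25.0 cm^2^ × number. of size-4 holes". The weighting rule is "The holes will be weighted according to the average area of each hole category", and the plan adds that "the weights would be 1, 23, 196 and 578, which corresponds with the areas estimated on the assumption" that hole sizes equal the class mid-points.
- **Nets with any holes.** The entry reads "Numerator: fabric integrity will be defined using the pHI [14] grouped into the following categories", followed by good, acceptable and torn.
- **Torn nets.** The definition given is headed poor condition. It counts nets too short to tuck in, nets that are torn or badly damaged, and nets that "have more than 5 holes (finger-width, approximate diameter 2 cm".

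The endpoint section (Secondary: fabric integrity) fixes the proportionate Hole Index (pHI) categories as "good (pHI range 0 to 64), acceptable (pHI 65 to 642) and torn (≥643". The Net survival section uses the same cut-offs: good and acceptable nets hung over a bed form the survivorship numerator, and torn nets enter attrition rate-1. The sample-size rationale for fabric integrity is built on 25% of nets in poor condition.

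**The concern.** A weight that represents average hole area should be recoverable from the class limits. With limits in cm², the second class should weigh about five times the first, not 23 times, and the third about 14.5 times, not 196 times. Either the unit or the weights must be wrong.

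The cut-offs of 64 and 642 are applied to the weighted sum, so a mismatch between how holes are sorted and how they are weighted moves nets across categories. Those categories define the secondary endpoint and enter two of the net-survival indicators. The protocol also offers itself as an exemplar for other durability studies, so the formula may be copied.

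The two companion indicators raise a separate reporting problem. One cannot take any value but 100% as written. The other is announced under a name that has a different definition elsewhere in the protocol.

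**Working it through.** **Inputs.** Class limits 0.5–1.9, 2.0–9.9, 10.0–24.9 and ≥25.0, and weights 1, 23, 196 and 578 (Data analytical plan, Fabric integrity). Cut-offs 64 and 642 (Secondary: fabric integrity). The top class is open-ended and the documents give no representative size for it, so any value is an assumption.

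**Step 1: classes as printed, in cm².** The weight is the mid-point area relative to class 1.
- Mid-points: (0.5+1.9)/2 = 1.2; (2.0+9.9)/2 = 5.95; (10.0+24.9)/2 = 17.45.
- Ratios: 5.95/1.2 = 4.96; 17.45/1.2 = 14.5.
- Stated weights against these: 23/4.96 = 4.6 times too large; 196/14.5 = 13.5 times too large.
- Top class: an assumed mean of 25 to 100 cm² gives a weight of 21 to 83. To reach 578 the mean hole would have to be 578 × 1.2 = 694 cm².

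The stated weights are not reproduced.

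**Step 2: same limits read as diameters in cm.** Circle area is proportional to diameter squared, so the weight is (mid-point/1.25)², with the classes taken as contiguous (0.5–2, 2–10, 10–25; mid-points 1.25, 6, 17.5).
- Class 2: (6/1.25)² = 23.04 (stated 23).
- Class 3: (17.5/1.25)² = 196.00 (stated 196).
- Class 4: at an assumed 30 cm, (30/1.25)² = 576 (stated 578; exactly 578 needs 30.05 cm). At 25 cm it is 400 and at 35 cm it is 784.

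Classes 2 and 3 fit with no assumption about the top class. Contiguous limits do not rescue the area reading: 6/1.25 = 4.8 and 17.5/1.25 = 14.

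**Step 3: effect if holes are sorted by area as printed.** A hole of area a has diameter 2√(a/π).

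| Net | Diameter of each hole | Score, area classes | Score, diameter classes |
|---|---|---|---|
| 2 holes of 25 cm² | 5.64 cm | 2 × 578 = 1,156 (torn) | 2 × 23 = 46 (good) |
| 4 holes of 10 cm² | 3.57 cm | 4 × 196 = 784 (torn) | 4 × 23 = 92 (acceptable) |
| 3 holes of 9 cm² | 3.39 cm | 3 × 23 = 69 (acceptable) | 3 × 23 = 69 (acceptable) |

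On the diameter scale one index unit is π × 0.625² = 1.227 cm², so the torn threshold of 643 is about 789 cm² of hole. The first net has 50 cm². The last row shows that not every net is affected.

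**Step 4: companion indicators.**
- Any holes: good (which includes pHI 0), acceptable and torn together exhaust the assessed nets. Numerator equals denominator, giving 100%.
- Torn or poor condition: six holes of 2 cm diameter exceed five, so the net is in poor condition. By diameter each is class 2; by area each is π × 1² = 3.14 cm², also class 2. Both readings give 6 × 23 = 138, which is acceptable, not torn.

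**The case against.** The best reply is that the superscript is a unit slip and nothing more. The same section describes finger-width holes by their diameter, and its wording about areas being estimated from mid-point hole sizes suits linear sizes converted to areas. The survey form is not shown, and the field section says only that holes are counted by location and size. If staff measure diameters, the weights and cut-offs work as they stand. This stands as a limit on the consequence, but it does not remove the printed inconsistency.

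A reader might infer that sound nets are in fact being classed as torn. The documents do not support that, because nothing shows that holes are sorted by measured area. A reader might also blame the two companion numerators for misclassified nets. They are separate reporting indicators and feed neither the pHI nor the survivorship categories.

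On poor condition, the definition is usable and broader than torn, since it includes torn nets. The sample-size rationale uses the same term. Requiring poor condition to mean pHI ≥643 throughout would be a design preference. What remains is a label conflict with the announced indicator. It is also tempting to say that six 2 cm holes could score as little as 6. That needs holes below 2 cm on the diameter classes and rests only on the word approximate.

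Finally, both arms share the rule, field workers are blinded, and the plan expects no difference between nets of the same fibre and weave. No directional bias between arms is shown.

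**Conclusion.** The printed classes and weights cannot both be right. This follows from the protocol's own figures for classes 2 and 3; only the fourth weight needs an assumed size of about 30 cm. The evidence points to diameters in cm as the intended scale.

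The harm is conditional. If holes are sorted by area, individual nets can move from good to torn, and the absolute torn, survivorship and attrition rate-1 figures become unreliable. If diameters are recorded, only the unit needs correcting. The between-arm comparison is less exposed than the absolute proportions.

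The any-holes numerator is wrong as written under either reading. The torn and poor-condition labels conflict, but each has a workable definition. The points touch a secondary and a tertiary outcome; bio-efficacy, the primary endpoint, is measured in the other village and is unaffected. This should be fixed.

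**What to change.** 1. State the four classes as diameters in cm, keeping the existing weights and cut-offs, and confirm that the survey form records diameters. The alternative is to keep area classes and recompute both the weights and the cut-offs.
2. Define the any-holes numerator as nets with at least one hole in any size class.
3. Label the first indicator poor condition, report torn (pHI ≥643) as a separate proportion, and state which of the two the 25% criterion in the sample-size rationale refers to.

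If diameters have been recorded, the cost is wording in the protocol and on the form. If holes have been tallied into area classes, rewording cannot re-sort those counts. Distribution was intended to finish by July/August 2014 and the article appeared in April 2015, so the baseline and 6-month surveys may already be done. The form should therefore be checked first.
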